### Health and lifestyle questionnaires

#### Demographics

Demographics will be collected by self-report including gender, age, ethnicity, marital status, education, employment status, return to work status and annual income. Medical variables, abstracted from chart reviews by study staff, will include specific diagnosis (type, stage, initial or recurrence), time since diagnosis, and current treatment.

### Physical activity behaviour

PA will be assessed using Godin’s leisure score index (LSI) of the GLTEQ (Godin Leisure Time Exercise Questionnaire)
[33]. The LSI is a 3-item measure assessing the frequency and duration of mild, moderate and strenuous bouts of exercise performed during free time in a typical week. In this study, participants will be asked to recall their exercise levels over the past month. The LSI has been successfully used with adult cancer patients and survivors, and has good reliability and validity as indicated by an independent evaluation to nine other self-report measures of exercise
[34-36].

### Patient-reported outcomes

#### Quality of life

QoL will be assessed using the Functional Assessment of Cancer Therapy- Anemia module (FACT-AN), and the NCCN-FACT Fact Head/Neck Symptom Index-22 (FHNSI-22). These tools examine the 5 major subsets of well-being for cancer survivors, including physical well-being, social/family well-being, emotional well-being, functional well-being, and additional concerns specific to HN cancer survivors. Based on these scales, the Trial Outcome Index (TOI) will be calculated, providing a final score based on the sum of the subscales.

#### Depression

Depression will be assessed using the Center for Epidemiological Studies on Depression Scale (CES-D). This 20-item questionnaire screens for self-reported depressive symptoms
[37]. It has shown excellent internal consistency in the cancer population with perfect sensitivity and strong specificity in a study of 33 cancer patients
[38].

#### Smoking history

Smoking history will be assessed by a self-report questionnaire. This questionnaire will classify patients as non-smokers, former smokers and current smokers.

#### Weekly PA logs

Participants will complete daily PA logs. These logs will highlight daily activities, the intensity of those activities (1-10 Rated Perceived Exertion Scale), and the duration of those activities.

#### Biweekly Edmonton symptom assessment system (ESAS)

Participants will complete the ESAS bi-weekly, before and after class. The ESAS is a valid and reliable assessment tool to evaluate the nine more common symptoms experienced by cancer patients
[39].

#### Diet behaviour

Diet will be assessed using a 3-day Diet Record once per month, and the PG-SGA will be completed once per week. The 3-Day Diet Record is said to be the most accurate for mean macronutrient content and appropriate for use in studies where subjects may consume a wide variety of foods
[40,41]. Participants are instructed to record their daily consumption, including alcohol intake, over a period of three days, one of which must be a weekend day. Written instructions and a sample entry are provided to increase accuracy of the daily record. The PG-SGA assessment tool has been show to improve treatment outcomes, decrease side-effects, and improve weight-management in cancer patients, and therefore will be used weekly to assess and identify malnutrition among patients
[31,32].

### Health-related fitness assessments

#### Body composition

Standing height and weight will be measured on a Heath Carter balance beam scale. Participants will be weighed weekly during active treatment and during the lifestyle intervention and maintenance phase. Weight will also be tracked at each of the 5 assessments. Waist circumference will be measured with an anthropometric tape measure at the top of the iliac crest and hip circumference will be measured at the greatest girth of the gluteus with the participant standing erect
[42]. Waist to hip ratio and body mass index (kg × m^-2^) will be calculated
[43]. A DXA scan (Hologic QDR 4500; Hologic Inc, Bedford, MA) will be performed a total of five times, at each assessment. Hologic QDR software will be used to determine lean mass, fat mass and bone mineral density. The DXA scans will be done at the Human Performance Laboratory at the University of Calgary.

#### Cardiorespiratory fitness

Although aerobic fitness is not the specific focus of the exercise intervention, the resistance training may likely have ancillary impact on cardiorespiratory fitness. While a submaximal cardiorespiratory test would be the standard, due to the limitations in this patient population, a functional measure of aerobic fitness was deemed to have greater value, as well as be more reflective of the training focus in the intervention. Resting heart rate will be measured using a heart rate monitor (Polar) and resting blood pressure (mmHg) will be measured in duplicate on the left arm using a sphygmomanometer and stethoscope using standardized procedures
[43]. Rating of perceived exertion (Borg scale) will be completed immediately prior to and immediately after completion of the functional aerobic capacity test. The six-minute walk test (6MWT) will be used to assess changes in functional aerobic capacity. Using the standardized protocol, participants will be asked to walk as far as they can around a 400-meter track for six minutes
[43]. The point reached at 6 minutes will be marked and measured to the nearest 0.5 meter. Post-exercise HR and BP will be measured one minute after a standard cool-down and after sitting quietly for five minutes before dismissal from the fitness-testing laboratory.

#### Musculoskeletal fitness

Muscular strength will be assessed using a combined grip strength of the right and left hands using a hand dynamometer. A sum will be determined in kilograms from the best score of 2 trials recorded for each hand according to the CPAFLA protocol
[43]. Lower body strength will be assessed using a 30-second sit to stand test. The number of times participants can stand from a seated position in 30-second will be examined
[44].

#### Flexibility

Flexibility will be assessed by a trunk forward flexion sit-and-reach test using a Wells-Dillon flexometer. The test will follow a standard protocol, with two trials allowed and the highest score to the nearest 0.5 cm recorded
[43].

#### Balance

Balance will be assessed using a static balance test. The test requires the participant to balance on one foot and then the other as long as they can (length of time) while standing on a 2.54 by 2.54 by 30.5 cm base using a standardized protocol, reported by Fleishman
[45].

### Measures of physical functioning

#### Participant performance score

The Karnofsky Performance Score (KPS) will be used to measure the participant’s general ability to accomplish tasks of daily-living and overall well-being. The Score is used to reflect the patient’s performance or function and ability to work, and is practical, objective, and has been validated and used for the past 50 years
[46].

### Blood data collection

#### Inflammatory markers

Inflammatory factors will be evaluated as they are associated with cancer cachexia and muscle wasting and may be modified by exercise
[47,48]. An overnight fasted blood draw will be collected at baseline, 3 months post diagnosis, 6 months post diagnosis, 9 months post diagnosis, and 12 months post diagnosis. Once further funding is secured, serum inflammatory cytokine concentrations will be assessed in-house ([name] laboratory) according to our established protocols. TNF, IL-6, IL-1, IL-8 and C-reactive protein will be quantified using Milliplex Human Cytokine kits (Millipore, Billerica, MA). Plate reading will be provided as a fee-for service through Eve Technologies Inc. (Calgary, AB).

### Sample size calculation

Sample size calculations are based on minimum participants required for a linear mixed models analysis as derived from Schmitz et al.
[27]. They suggest a strong relationship between strength training and improvements in lean tissue in cancer patients. The power calculation was derived using G-Power
[49,50]. The effect size of 0.63 was calculated based on relevant literature associated with similar interventions and α = 0.05 and β = 0.80 were used
[22,27]. Based on these numbers, it was determined that a power of n = 32 is required for each group. Accounting for potential participant drop-out, a 20% buffer will be added and a total of n = 40 for each group, for a total n = 80. All intervention participants will be recruited for the intervention over year one of the study. Preliminary data from the EHNANCE exercise program for HN patients indicates that this recruitment goal is feasible (36 patients recruited in 4 months, with adherence at 90%).

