The purpose of this proposed research is to examine the immediate and long term physical and psychosocial benefits of a clinic-supported physical activity and nutrition program during and after treatment for HN cancer survivors, and to investigate the clinical implications associated with increasing the promotion of healthy lifestyle behaviors for this population. This research will address the pressing need for clinic-supported HN cancer lifestyle interventions that effectively demonstrate physical and psychosocial patient benefit.

Specifically, this study is designed to examine the potential benefits of a lifestyle (PA, nutrition, and health education) intervention. Specific objectives include the following:

1. Whether a lifestyle intervention will improve outcomes, including physiological (muscle mass maintenance), fitness, psychological (QoL and depression), smoking status, inflammatory markers, and functional (return to work).

2. Whether it is optimal, in terms of outcomes, to deliver the program during or after treatment completion.

3. Whether a survivorship care plan (SCP) maintenance program improves long-term healthy lifestyle adherence.

Without exploration into these questions, HN cancer care will continue to only partially serve patients in their quest towards healthy cancer recovery, strong physical functioning ability, improved QoL, and timely return to work. These studies will provide concrete evidence for a clinic-supported lifestyle intervention and maintenance program as a means to mediate these currently unaddressed factors and improve functioning and psychosocial outcomes.

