### Analysis

Analyses will include feasibility (participants recruited; program attendance), descriptive analyses and statistical tests examining change over the program duration. The raw data will be analyzed using SPSS Version 19.0, and will primarily consist of linear mixed models. Information from the 3-Day Diet Records will be analyzed with Diet Analysis Plus 10.0 software (Wadsworth Inc.) to generate total daily energy intake, macronutrient and micronutrient intake for each participant. The resultant data will be analyzed using SPSS.

For the primary objective, we will be utilizing linear mixed models analyses, to examine change between groups and over time, with the primary outcome being body composition changes over time and between the two groups (immediate intervention and delayed intervention).

For the secondary objective, we will also examine change over time in health related fitness, QoL, functional status (Karnofsky), dietary intake, and markers of inflammation.

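### The 32 per group reproduces from the printed inputs as a one-sided 5% t-test; no one-sided test is declared, and a two-sided test would need 41

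*Protocol article*

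**What the plan says.** The section Sample size calculation describes the number as the minimum for a linear mixed models analysis. It gives three inputs and a tool:

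- Effect: "The effect size of 0.63 was calculated based on relevant literature associated with similar interventions". The metric is not named.
- Error rates: "α = 0.05 and β = 0.80 were used".
- Software: "The power calculation was derived using G-Power".

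The result reads "Based on these numbers, it was determined that a power of n = 32 is required for each group", and it is raised to 40 per group and 80 in total for 20% drop-out. The section gives no sidedness, within-patient correlation or number of repeated measurements.

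The Analysis section says that the analyses "will primarily consist of linear mixed models". The primary outcome there is body composition change over time between the immediate and delayed groups. It does not state sidedness either.

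**The concern.** The article presents 32 as following from its printed inputs. Under the ordinary two-sided reading of α = 0.05 it does not. Under a one-sided reading it does, but that choice is not declared, and parts of the article point the other way. The second objective in the Background asks "Whether it is optimal, in terms of outcomes, to deliver the program during or after treatment completion", which is open in both directions. The section Protection against bias says participants will be told that the effect of timing is not yet known.

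Two wording errors add to the uncertainty. A β of 0.80, taken literally, means 20% power. The result sentence also calls a sample size a power.

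At stake is how a null result would be read. If the primary test is two-sided and has no gain from repeated or baseline measurements, a true effect of 0.63 would be missed about 30% of the time among 32 completers per group, and not 20%.

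**Working it through.** **Inputs.** Effect size 0.63, read as a standardised mean difference d (an assumption, since the metric is not named); α = 0.05; power 0.80, reading the printed β as power; 1:1 allocation (Protection against bias); 20% drop-out.

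**Model.** Two independent groups of n, noncentral t with 2n − 2 degrees of freedom and noncentrality d·√(n/2).

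**Step 1: reproduce the article's figure.** At n = 32 the noncentrality is 0.63 × √16 = 2.52. The one-sided 5% critical value on 62 degrees of freedom is 1.670.

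- One-sided power: 79.0% at n = 31 and 80.2% at n = 32.
- Required n = 31.85, rounded up to 32. This matches.
- Drop-out: 32/0.8 = 40 per group, 80 in total. This step is correct.

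**Step 2: the same inputs, two-sided.** The critical value at n = 32 becomes 1.999.

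| Evaluable per group | Two-sided power for d = 0.63 |
|---|---|
| 32 | 69.9% |
| 40 | 79.5% |
| 41 | 80.5% |

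Required n = 40.53, rounded up to 41. With 20% drop-out, 41/0.8 = 51.25, so 52 per group or 104 in total. At 32 evaluable per group, 80% two-sided power is reached at d = 0.71.

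The normal approximation, n = 2(z₁ + z₂)²/d², agrees: 31.2 (32) one-sided and 39.6 (40) two-sided, with 71.2% two-sided power at 32.

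**Step 3: can 32 arise from a two-sided test?** Yes, but only with added inputs. All correlations below are assumptions; the article gives none.

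*Repeated-measures between-group test.* Take f = 0.63/2 = 0.315, m measurements and common correlation r. The noncentrality is λ = N·f²·m/[1 + (m − 1)r].

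| m | r | Total N for 80% power |
|---|---|---|
| 5 | 0.3 | 38 |
| 5 | 0.5 | 50 |
| 5 | 0.7 | 64 |
| 4 | 0.7 | 64 |

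For m = 4 and r = 0.7, λ = 64 × 0.099225 × 4/3.1 = 8.19, and power is 80.5%. So a total of 64 (32 per group) appears at r = 0.7 with either all five assessments or the four after baseline.

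*Baseline-adjusted comparison (ANCOVA), if 0.63 is in raw SD units.* The effective d is 0.63/√(1 − r²). Two-sided power at 32 per group is 74% at r = 0.3, about 80% at r = 0.46, 82% at r = 0.5 and 93% at r = 0.7.

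*Change score, if 0.63 is in raw SD units.* The effective d is 0.63/√[2(1 − r)]. Power at 32 is 55% at r = 0.3, 70% at r = 0.5, 79% at r = 0.6 and 89% at r = 0.7. If 0.63 is already standardised on change, a change-score analysis gains nothing and power stays at 69.9%.

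**The case against.** The strongest reply is that the article sizes the trial for a linear mixed model, so a single-time-point t-test is the wrong yardstick. The figure of 32 has more than one possible origin: a two-sided repeated-measures test with r = 0.7 also gives 64 in total. Body composition is measured by DXA at baseline, so adjustment could recover power. A mixed model can also use partial follow-up from drop-outs, so 70% is a completers-only figure and 79.5% applies if all 40 per group contribute fully. The hypotheses in the Background are directional, and a condensed article may leave correlation inputs to the full protocol.

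Most of this stands, and it limits the point. A reader might infer that 32 can come only from a one-sided test, or that the trial certainly lacks its stated power. The article supports neither: sidedness, the metric of 0.63 and any correlation are all unstated. The absence of a correlation from a condensed article is not a fault in itself.

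The reply does not rescue the text as printed. The article says 32 follows from the numbers it lists, and the two-sided routes need a number it does not list. The repeated-measures route reaches 64 only near r = 0.7. With five measurements it includes the baseline, where no effect is expected. With four it assumes a constant difference, although the delayed arm starts the programme at about 12 weeks. A directional hypothesis is also not a declaration of a one-sided test.

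**Conclusion.** The point holds as an error in the sample size statement. From the printed inputs, 32 per group is the one-sided 5% two-sample t-test answer, and no one-sided test is declared. Two-sided, the same inputs need 41 evaluable per group, with about 70% power at 32 completers and about 79.5% at 40. These figures rest on reading 0.63 as d, reading the printed β as power, and taking no gain from baseline or repeated measurements. If any of these differs, so does the power; the power of the planned mixed model is undetermined from the article. The mislabelled β and the sample size called a power are wrong on any reading.

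**What to change.** Keep N = 80 and amend the section Sample size calculation:

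1. Replace the β value with *power (1 − β) = 0.80*, and call 32 *a sample size of n = 32*.
2. State the test and its sidedness, and name the metric of 0.63.
3. If the test is two-sided with no correlation assumed, write: *For a two-sided 5% two-sample comparison, 32 evaluable participants per group give 70% power for d = 0.63 and 80% for d = 0.71; 40 per group give about 79.5% for d = 0.63.*
4. If a one-sided test or a correlation-based mixed-model calculation was intended, say so with its inputs, and specify the same test for the primary analysis in the Analysis section.

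The cost is wording only. Under item 3 the stated power becomes less favourable.

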### Analysis

Analyses will include feasibility (participants recruited; program attendance), descriptive analyses and statistical tests examining change over the program duration. The raw data will be analyzed using SPSS Version 19.0, and will primarily consist of linear mixed models. Information from the 3-Day Diet Records will be analyzed with Diet Analysis Plus 10.0 software (Wadsworth Inc.) to generate total daily energy intake, macronutrient and micronutrient intake for each participant. The resultant data will be analyzed using SPSS.

For the primary objective, we will be utilizing linear mixed models analyses, to examine change between groups and over time, with the primary outcome being body composition changes over time and between the two groups (immediate intervention and delayed intervention).

For the secondary objective, we will also examine change over time in health related fitness, QoL, functional status (Karnofsky), dietary intake, and markers of inflammation.

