#### Treatment arms

Once enrolled, the participant will be randomized to either begin the intervention at the time of treatment initiation (ILI, n = 40), or to begin the intervention following treatment completion (DLI, n = 40). Patients will be recruited, cleared for participation, receive an initial assessment, and then be randomized into either the ILI group or the DLI group. Participants in the ILI group will receive an individualized exercise and dietary program based on their exercise assessment and dual energy x-ray absorptiometry (DXA) scan results, will attend twice weekly group exercise classes, and perform their individualized at-home program an additional two times per week. In addition, participants will be required to attend six education sessions during the 12-week intervention. The DLI group will receive this intervention upon their treatment completion, at approximately 12-weeks post-randomization.

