### Measures

The assessments will consist of a battery of patient-reported instruments to assess demographics, medical information, PA and dietary behavior, QoL, depression, smoking status as well as a physical fitness assessment and a comprehensive body composition assessment. Inflammatory markers, including TNF, IL-6, IL-1, IL-8 and C-reactive protein will be assessed in serum. A chart review will also be conducted to assess diagnosis, treatment plan and outcomes. The assessment will take approximately 1.5 hours to complete and will occur at baseline (time of diagnosis), 3, 6, 9, and 12-months post diagnosis.

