### Protection against bias

To protect against bias, participants will be randomly assigned to one of the two intervention arms, using randomization.com, a web-based random number generation program with a 1:1 allocation ratio. Exercise testers who will be evaluating participant fitness measures will be blinded to participant allocation. When participants are recruited, they will be told that there is an equal possibility that they will be assigned to one of the two groups (immediate lifestyle intervention or the delayed lifestyle intervention group) and that the impact of intervention timing is not yet known. Once they have completed their initial assessment, they will be contacted by the research coordinator and told which group they have been allocated and receive an explanation of the protocol and their responsibilities.

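### The mixed models of change do not say that they adjust for the pre-randomisation baseline; adjusting would gain precision at almost no cost, probably little for lean mass and more for quality of life, fitness and function

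*Protocol article*

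**What the plan says.** For the primary objective, the Analysis section of the protocol article names linear mixed models "to examine change between groups and over time". The primary outcome is change in body composition, compared between the immediate (ILI) and delayed (DLI) arms. For fitness, quality of life, Karnofsky score, diet and inflammatory markers, the same section says only that change over time will be examined.

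Under Treatment arms, patients "receive an initial assessment, and then be randomized into either the ILI group or the DLI group", so the first measurement comes before allocation. Under Measures, the assessments "will occur at baseline (time of diagnosis), 3, 6, 9, and 12-months post diagnosis", so baseline is one of five visits. Under Study design, the DLI arm is the control only during the first 12 weeks. Treatment arms then gives it the same programme from about 12 weeks after randomisation.

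The article does not say whether baseline is a covariate, a response with a common mean across arms, a response with a separate mean in each arm, or simply the value that is subtracted.

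**The concern.** Because baseline is measured before randomisation, the two arms have the same expected baseline. A model that gives each arm its own baseline mean, or that analyses change scores, ignores this. With complete data, both lead to the same 3-month contrast: the unadjusted difference between arms in mean change. That estimate is unbiased under randomisation, but it carries the full noise of the baseline measurement. Regressing on baseline, or constraining the baseline means to be equal, removes part of that noise.

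With 40 patients per arm planned and 32 per arm left after the dropout allowance, a wider standard error than necessary is a real loss, and the data needed to avoid it are already being collected. Bias and validity are not at stake.

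**Working it through.** **The plan's own figure.** From Sample size calculation: "The effect size of 0.63 was calculated based on relevant literature associated with similar interventions"; "α = 0.05 and β = 0.80 were used" (0.80 is read as power); "it was determined that a power of n = 32 is required for each group"; "a 20% buffer will be added and a total of n = 40 for each group, for a total n = 80". Allocation is "with a 1:1 allocation ratio" (Protection against bias).

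- Formula: n per arm = 2(z_alpha + z_power)² / d², with d = 0.63.
- One-sided 0.05: 2(1.645 + 0.842)² / 0.63² = 31.2, so 32. This reproduces the plan. The exact t calculation also gives 32.
- Two-sided 0.05: 2(1.960 + 0.842)² / 0.63² = 39.6, so 40 (41 by exact t). This does not reproduce the plan.
- Dropout: 32 / (1 − 0.20) = 40 per arm.

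The article states no sidedness. With 32 per arm, power is about 80% one-sided and about 70% two-sided.

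**Variance of the 3-month contrast.** Let the outcome have variance σ² at both visits and correlation r between them.

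- Change score: variance per patient σ² + σ² − 2rσ² = 2σ²(1 − r).
- Baseline-adjusted: σ²(1 − r²).
- Ratio, adjusted to change: (1 − r)(1 + r) / [2(1 − r)] = (1 + r)/2.

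The direction does not depend on equal variances. With baseline SD σ0 and follow-up SD σ1, the change variance minus the adjusted variance is (σ0 − rσ1)², which is never negative.

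**Numbers.** The documents give no r, so every value below is an assumption. The power columns use 32 per arm, the normal approximation, and an effect of 0.63 taken in units of the SD of change; the article does not say which SD it means.

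| r (assumed) | Variance ratio | Variance reduction | SE reduction | Power, one-sided (unadjusted 0.81) | Power, two-sided (unadjusted 0.71) |
|---|---|---|---|---|---|
| 0.3 | 0.65 | 35% | 19% | 0.93 | 0.88 |
| 0.5 | 0.75 | 25% | 13% | 0.90 | 0.83 |
| 0.7 | 0.85 | 15% | 8% | 0.86 | 0.78 |
| 0.9 | 0.95 | 5% | 2.5% | 0.83 | 0.73 |
| 0.95 | 0.975 | 2.5% | 1.3% | 0.82 | 0.72 |
| 0.98 | 0.99 | 1% | 0.5% | 0.81 | 0.72 |

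**Check by simulation.** With 4000 simulated trials of 32 per arm, the variance ratios were 0.665, 0.756, 0.858 and 0.989 at r = 0.3, 0.5, 0.7 and 0.95, against 0.65, 0.75, 0.85 and 0.975 in theory. Both estimators centred on the true effect. The small excess over theory is in line with the price of estimating the baseline slope, a factor of about 1 + 1/(64 − 4) = 1.017 with 64 patients. At r = 0.98 that price cancels the gain (0.99 × 1.017 = 1.007).

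**The case against.** The strongest objection is that this is a condensed article. How baseline enters a mixed model is often left to the full protocol or analysis plan, and neither is shown. The wording is compatible with a common baseline mean or a baseline covariate, and in that case the gain is about zero. This stands to the extent that one cannot say that the plan rejects adjustment. However, the article does fix its models as models of change between groups and over time, with baseline among the visits. The ordinary reading of that is the unadjusted comparison.

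A second objection also stands. The quoted sentence concerns body composition, where r is probably high and the gain slight. The outcomes likely to gain more are in the next paragraph, which gives no model form of its own. The ranking of outcomes rests on assumed correlations.

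Four stronger readings are tempting, but the documents do not support them:

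- A reader might infer that the baseline goes unused. A model of change uses it in some form; what is not stated is adjustment.
- A reader might infer that the effect is diluted by averaging over all five visits, including baseline. The plan proposes no such pooled group effect. A constant effect is also not to be expected once the DLI arm receives the programme.
- A reader might infer that the trial has only about 70% power. That holds only for a two-sided test.
- A reader might infer that simple randomisation makes baseline imbalance especially likely. The article names a web-based generator and a 1:1 ratio, and does not say whether allocation is simple or blocked. In any case, chance imbalance is already counted in the variances above and is not an additional harm.

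**Conclusion.** The point holds as an available gain in precision, not as an error. On its natural reading the analysis is valid and unbiased, but its variance is 2/(1+r) times that of a baseline-adjusted analysis. For outcomes with r of 0.3 to 0.7, plausible for quality of life, fitness and function, adjustment would cut the variance by about 15% to 35%. For DXA lean mass, with r plausibly 0.9 to 0.98, the cut is about 1% to 5% before the small cost of estimating the slope, so the primary result would hardly change.

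These sizes rest on assumed correlations, on equal variances at the two visits, and on the model not already having a common baseline mean. The power figures rest in addition on reading 0.63 in SDs of change.

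**What to change.** For each continuous outcome measured at baseline, state that the mixed model constrains the baseline mean to be equal across arms. Equivalently in purpose, take the 3-, 6-, 9- and 12-month values as outcomes with the baseline value as a covariate. In either form, enter visit as a category and include arm-by-visit terms.

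Read the immediate-versus-delayed effect from the arm contrast at 3 months, which closes the only period in which the DLI arm is a control. The same model supplies the later contrasts for the timing question.

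The cost is a sentence or two in the Analysis section and about one degree of freedom per outcome. No new data are needed, and SPSS, the package already named, can fit the model. If a common baseline mean is already intended, saying so settles the point.
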